### Control: Standard care

Participants in the control group will receive standard care only with no IVR intervention during their chemotherapy. Standard care consists of pre-chemotherapy instruction and intravenous antiemetic administration as needed.

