### Implementation protocol

A trained research assistant (RA) provides the patients with standard instruction on how to use the IVR equipment in the first session. The Google cardboard goggles will then be placed and adjusted on the patient’s head to ensure comfort and secure fit. For the first session, patients are given 30 minutes to use and familiarise themselves with the IVR equipment [17, 18].

For the second and third sessions, the RA provides IVR to patients 5 minutes before the chemotherapy commences [2, 19]. The RA asks the oncology nurse to start the administration once the patients are ready for the chemotherapy treatment. The nurse first disinfects outlets of the intravenous site, connect the device and start infusion, during which patients will be allowed to view their selected VR modules or take off the headset at will. The RA will record the time of each module used by the patients by using a time-counting device. When the infusion is over, the RA will remove the IVR equipment.

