### Procedures

A nurse in the paediatric oncology unit will screen for eligibility for all patients who are admitted to receive their first intravenous chemotherapy during pre-chemotherapy assessment. If children meet the inclusion criteria, the nurse will refer them and their accompanying parents to the RA who will give them an information sheet, explain the trial and show the IVR equipment. If they agree to participate, an informed consent will be obtained from the accompanying parents. The RA will then acquire socio-demographics and clinical characteristics of the patients from medical record. According to the subject allocation, children in the control group will receive standard care, while the intervention group will additionally receive the IVR intervention.

Four hours prior to (T0), immediate before first course (T1), and second course of chemotherapy begins (T3), a set of data (i.e. anxiety, HR & BP and anticipatory CINV) will be collected from the patients. Immediate after the first (T2) and second course of chemotherapy (T4), the anxiety, HR & BP and acute CINV will be collected. In the intervention group, the timing and duration of IVR use and modules selected will also be recorded. The SPIRIT schedule of the trial is shown in Fig 1.

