**Fig 1 pone.0258514.g001:**
[figure not shown]
SPIRIT schedule of the trial. T0: Pre-test data 4 hours prior to chemotherapy; T1: Immediate before 1^st^ chemotherapy starts; T2: Immediate after 1^st^ chemotherapy; T3: Immediate before 2^nd^ chemotherapy starts; T4: Immediate after 2^nd^ chemotherapy. ^1^IVR: Immersive virtual reality; ^2^CSAS-C: The short form of the Chinese version of the State Anxiety Scale for Children’.

Individual face-to-face semi-structured interviews will be conducted at T4 with patients in the interventional group, their accompanying parents and oncology nurses involved in the chemotherapy administration. Frequency of vomiting will be obtained from medical record (T0-T4). All children will be given the Google cardboard goggles after the completion of trial. The flow diagram of trial design is shown in Fig 2.

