### Data analysis

IBM SPSS for Windows (Version 26) will be used. Appropriate descriptive statistics will be used to summarise data such as screening, eligibility, consent and withdrawal rates.

Continuous demographic (e.g. age) and clinical variables (e.g. scores on CSAS-C) will be presented by their means and standard deviations, whereas categorical data (e.g. sex) will be presented in frequencies and percentages. Pearson’s chi-square test (or Fisher’s exact test) and independent t-test (or Mann-Whitney test for highly skewed data) will be used as appropriate for assessing the homogeneity of the baseline characteristics of the two groups. The intention-to-treat principle will be adopted in the outcome evaluation between the two groups [25]. Generalized estimating equations model will be used to compare each of the outcome measures across the time points between the two groups. GEE model can account for intra-correlated repeated measures data and produce unbiased estimates even in the presence of missing data, provided they are missing at completely random. Potential confounders on the outcome variables, including duration of IVR used, will be adjusted in the GEE models to improve the precision of the effect estimates. Cohen’s d values will also be calculated to estimate the effect sizes of the IVR intervention on the outcome variables. All statistical analyses are two-sided and level of significance will be set at 0.05.

All interviews will be transcribed verbatim into written Chinese before conventional content analysis is conducted. Starting with line-by-line coding, statements that are related to (1) the acceptability and feasibility of the intervention and (2) acceptability and feasibility of trial procedures will be coded and categorized. Once the categories have ample data, they will be broken down into sub-categories. The categories and subcategories will be reviewed by two co-investigators to ensure participants’ points of views are accurately reflected. Appropriate strategies will be undertaken to ensure the trustworthiness including credibility, dependability, confirmability, and transferability [27].

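### The GEE group comparison is to be adjusted for duration of IVR use, which is treatment received after randomisation (zero in every control), not a confounder

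*Protocol article*

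**What the plan says.** All references are to the protocol article.

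- Data analysis gives the model and the contrast: "Generalized estimating equations model will be used to compare each of the outcome measures across the time points between the two groups". It also states: "The intention-to-treat principle will be adopted in the outcome evaluation between the two groups".
- The same paragraph names the covariate and its purpose: "Potential confounders on the outcome variables, including duration of IVR used, will be adjusted in the GEE models to improve the precision".
- Control: Standard care: "Participants in the control group will receive standard care only with no IVR intervention during their chemotherapy". Controls are offered the headset only later; Procedures (text after the Fig 1 legend) says: "All children will be given the Google cardboard goggles after the completion of trial".
- Procedures: "In the intervention group, the timing and duration of IVR use and modules selected will also be recorded".
- Implementation protocol: during the infusion "patients will be allowed to view their selected VR modules or take off the headset at will". The equipment is removed when the infusion ends.

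Nothing in the article limits the adjustment to a secondary or within-arm analysis. It does not say whether duration enters as one total per child or visit by visit, whether it is centred within the IVR arm, or which model term carries the treatment effect.

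**The concern.** A confounder of a randomised comparison would have to be related to allocation without being caused by it. Minutes of IVR are caused by allocation. They are the dose of the randomised treatment, fixed at zero in one arm and, in the other, dependent on the child's wishes and on infusion length. A model containing both group and minutes no longer asks what being allocated to IVR does. Its group coefficient is the fitted difference between an IVR-arm child who used no IVR and a control. That is not the effect the intention-to-treat statement leads the reader to expect.

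The stated reason, better precision, is doubtful too, because a variable that is zero in one arm and positive in the other is collinear with group. At stake are the preliminary between-group results on anxiety, physiological measures and CINV, which are meant to inform a definitive trial. An artefactual null could discourage that trial.

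**Working it through.** The plan has no figure to reproduce: it gives no effect size, SD, power or expected duration. The numbers below rest on stated assumptions.

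**Inputs.** From the article: 20 patients, no IVR in controls, anxiety and HR/BP measured at T0 to T4, anticipatory CINV at T0, T1 and T3, acute CINV at T2 and T4 only. Inferred: 10 per arm (the ratio is not stated, but 10 intervention patients are to be interviewed). Assumed: true total effect -0.8 SD; coefficient of variation (CV) of IVR minutes 25%, 50% or 100%; and, for the distress scenario, a correlation of -0.5 between a child's outcome and minutes used.

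**Step 1: what the group coefficient estimates.** Only the IVR arm informs the slope on minutes, so by least squares at one time point

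adjusted group effect = (IVR mean - slope × mean minutes m) - control mean.

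- Benefit proportional to minutes: slope = -0.8/m, so the effect is -0.8 - (-0.8/m) × m = 0.
- Distressed children stop sooner: slope = -0.5/(CV × m) in SD units, so the effect is -0.8 + 0.5/CV. This is +1.2 at CV 25% and +0.2 at CV 50%.
- Minutes unrelated to outcome: slope = 0, so the effect stays at -0.8.

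**Step 2: precision.** With 1:1 arms and IVR-arm mean m and SD s, the R² of group with duration is (m²/4)/(m²/4 + s²/2) = m²/(m² + 2s²). Variance inflation is 1/(1 - R²) = 1 + 1/(2·CV²).

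- CV 25%: 1 + 1/0.125 = 9.0; SE × 3.00
- CV 50%: 1 + 1/0.5 = 3.0; SE × 1.73
- CV 100%: 1 + 1/2 = 1.5; SE × 1.22

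For a net gain, minutes would have to explain more than 1/(1 + CV²) of the IVR-arm outcome variance: about 94%, 80% and 50% respectively.

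**Step 3: simulation where the group term carries the effect.** Mean group coefficient (empirical SE), 10 per arm. Least squares (LS): 4,000 runs. GEE: two post-chemotherapy visits, exchangeable correlation, minutes entered per visit, 300 runs. At least one GEE fit stopped at its iteration limit, so those columns are approximate.

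| Assumed truth | CV | LS without | LS with | GEE without | GEE with |
|---|---|---|---|---|---|
| Proportional to minutes | 25% | -0.80 (0.44) | 0.01 (1.61) | -0.83 (0.45) | 0.03 (1.05) |
| | 50% | -0.80 (0.45) | 0.02 (0.88) | -0.80 (0.45) | 0.01 (0.67) |
| Unrelated to minutes | 25% | -0.80 (0.45) | -0.83 (1.61) | -0.81 (0.44) | -0.86 (1.07) |
| | 50% | -0.80 (0.45) | -0.79 (0.89) | -0.79 (0.46) | -0.81 (0.66) |
| Distressed stop sooner | 25% | -0.80 (0.45) | 1.18 (1.36) | -0.78 (0.44) | 0.79 (1.03) |
| | 50% | -0.80 (0.45) | 0.23 (0.79) | -0.80 (0.42) | 0.02 (0.67) |

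The least-squares results match Step 1. The loss of precision is smaller in the GEE than the single-time formula gives, but it remains: at CV 50%, with minutes unrelated to outcome, the SE is 0.66 against 0.46.

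**Step 4: outcomes with a T0 value, effect read from group-by-time.** Five-visit GEE, 10 per arm, minutes with mean 30 and SD about 15, 150 runs per setting.

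- One total per child: the T4 group-by-time estimate was the same with and without duration (-0.81 proportional, -0.86 constant effect, -0.83 distress), and so was its SE. A value constant within a child cancels from that child's change since T0; the distortion falls on the group main effect, which is the T0 contrast. With 10% of visits missing, the means still agreed to three decimals.
- Per visit, zero at T0: the estimate moved from -0.84 to -0.26 (proportional) and from -0.82 to -0.42 (distress), and the SE rose by about 23% to 38%.

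**The case against.** A reader might infer that every between-group estimate in the trial will be biased and less precise. The documents do not support that. The comparison is across time points, and anxiety, HR/BP and anticipatory CINV have a T0 value. If the effect is read from group-by-time terms and duration is a single total per child, Step 4 shows those terms essentially untouched. If minutes are unrelated to outcome there is no bias on average. If minutes were centred within the IVR arm and set to zero for controls, the group coefficient would equal the unadjusted one (-0.80 in the simulation). The article is silent on coding, centring and model terms, so these readings stay open. The near-zero and reversed figures rest on assumed mechanisms.

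Three further points stand. The trial is exploratory, and its screening, eligibility, consent and withdrawal rates and its interviews do not depend on this model. Children can still be analysed in their allocated group, so the conflict is with the intention-to-treat effect, not with the analysis set. The article does not say that Cohen's d will come from the adjusted model.

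None of this rescues the covariate. Acute CINV has no T0 value, so its group term carries the effect and is exposed under either uncentred coding. In the harmless case the adjustment does not deliver its stated purpose. Nor is this a detail left to an analysis plan: the article names the covariate, and a plan that followed it would inherit the problem.

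**Conclusion.** The point holds in conditional form. Duration of IVR use is not a confounder and should not be in the model that compares the groups. Where the group term carries the effect, or duration is entered per visit, the adjusted estimate can lose most or all of a real effect, can be reversed if distressed children stop sooner, and is less precise even when unbiased. With one total per child and group-by-time terms anchored at T0, the adjustment is inert and brings no precision gain. The sizes depend on the assumed -0.8 SD effect, the CV of minutes and the -0.5 correlation, none of which the article gives. The direction of the precision result needs only 1:1 arms, zero minutes in controls and a duration-outcome relation below the thresholds in Step 2.

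**What to change.** In Data analysis, delete the reference to duration of IVR used from the GEE adjustment. State that the between-group models adjust only for variables fixed before randomisation, such as the cancer-type stratum and the T0 value where one is measured, provided T0 is taken before allocation and is not already a modelled time point. State which term carries the treatment effect for each outcome.

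Report minutes used descriptively for the IVR arm as a feasibility and acceptability result, for example with minutes used as a share of minutes offered and sessions started. Label any analysis relating minutes to outcome as exploratory and confine it to that arm.

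The cost is a few lines of analysis text. Duration is already being recorded, so no new data are needed, and no result that the trial needs is lost.

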### Reporting guidelines

Standard Protocol Items: We adhered to the Recommendations for Interventional Trials reporting guidelines in this protocol [28].

### Ethics and dissemination

Ethical approval has been sought from the Hong Kong Children’s Hospital Research Ethics Committee with reference number: HKCE-REC-2019-007, on March 1, 2019. Written consent from parents and nurses, as well as assent from children will be obtained prior to study commencement. The findings will be disseminated in peer-reviewed journals and conference presentations.

## Discussion

Pre-chemotherapy anxiety and CINV are the most distressing side effects of paediatric cancer patients undergoing chemotherapy [3, 4]. In view of the negative impacts of unmanaged anxiety and CINV on patents, parents, and medical institutions, effective intervention to manage these symptoms is crucial. However, pharmacological treatments for CINV prevention are still suboptimal [5]. There has been some reports describing distraction and relaxation intervention to addressing the needs of this vulnerable group. However, distractors previously used did not provide complete distraction [9]. IVR allows the patient to be completely engage in an immersive environment, which may help distract the patient from noxious stimuli during chemotherapy, thereby reducing the distressing symptoms.

This exploratory trial aims to examine the acceptability and feasibility of IVR, a novel intervention for distracting paediatric cancer patients undergoing chemotherapy in Hong Kong. Interviews will also be conducted with patients, parents, and healthcare providers to assess satisfaction and any improvements. The mixture of quantitative and qualitative methods is essential to inform the feasibility of recruiting and retaining of patients, the acceptability of parents, parents, and healthcare providers, and to determine appropriate outcome measures that are important for design of definitive trial [27].

The results of this trial will shed light into the use of distraction and relaxation-based IVR intervention to alleviate the psychological and physical sufferings of paediatric cancer patients who require chemotherapy treatments. It will generate empirical evidence on the feasibility of IVR intervention in clinical practice. If feasible and acceptable, IVR may be considered to incorporate into the clinical settings to provide a convenient, attractive and easily applied intervention to distract and relax paediatric patients undergoing chemotherapy virtually at any time and place.

However, several limitations of this trial must be acknowledged. First, only paediatric cancer patients between the ages of 6–12 years will be recruited. Patients under six years of age who are prone to anxiety during chemotherapy will not be included. Therefore, the trial results may not be able to generalise to other age groups. Second, this trial will only be conducted in a single institution so contamination between intervention and control group cannot be ruled out. Nevertheless, the intervention will take place in the patients’ rooms to minimize potential bias. Finally, the trial will only examine the preliminary short-term effects of IVR intervention on anxiety and CINV outcomes (after the second chemotherapy). Therefore, the sustainability of IVR intervention over long periods cannot be determined.

In summary, the proposed IVR intervention will potentially provide insights into the feasibility and acceptability of IVR intervention in managing anxiety, nausea and vomiting among paediatric cancer patients receiving their first chemotherapy. The results will provide a foundation for future studies.

## Trial status

This article presents the protocol for the exploratory trial (original v1). The recruitment period started on May 2019. However, due to COVID-19, recruitment has been suspended since December 2019. At the time of the first version of manuscript submission, data collection was still ongoing.
